## TRIAL SCHEDULE

| Action                                                                  | Visits | V1
Screening  | Visit 2  | Visit 3    | Visit 4     | TC 4a  ☎ | Visit 5     | TC 5a  ☎ | Visit 6     | TC 6a  ☎ | Visit 7 (End of study) |
|-------------------------------------------------------------------------|--------|-------------------------------|---------------------------|------------|-------------|----------------------|-------------|----------------------|-------------|----------------------|------------------------|
| Trial day / week                                                        |        | -6 to -4 weeks                | 0                         | 6 ± 1 week | 16 ± 1 week | 22 ± 1 week          | 28 ± 1 week | 34 ± 1 week          | 40 ± 1 week | 46 ± 1 week          | 52 ± 2 weeks           |
| Patient information and informed consent                                |        | x                             |                           |            |             |                      |             |                      |             |                      |                        |
| Demographics (e.g. sex, age, race)                                      |        | x                             |                           |            |             |                      |             |                      |             |                      |                        |
| Previous and concomitant diseases                                       |        | x                             | x                         | x          | x           | x                    | x           | x                    | x           | x                    | x                      |
| Previous and concomitant treatments                                     |        | x                             | x                         | x          | x           | x                    | x           | x                    | x           | x                    | x                      |
| Inclusion/exclusion criteria                                            |        | x                             | x                         |            |             |                      |             |                      |             |                      |                        |
| Physical examination                                                    |        | x                             | x                         | x          | x           |                      | x           |                      | x           |                      | x                      |
| Vital signs (BP, pulse, temperature)                                    |        | x                             | x                         | x          | x           |                      | x           |                      | x           |                      | x                      |
| Height and weight                                                       |        | x                             | x                         | x          | x           |                      | x           |                      | x           |                      | x                      |
| Laboratory testing                                          |        | x                             |                           |            |             |                      |             |                      |             |                      | x                      |
| Spirometry/Oscillometry in patients ≥ 4 years pre-dosing  |        | x                             | x                         | x          | x           |                      | x           |                      |             |                      | x                      |
| Spirometry/Oscillometry pre and 30 minutes post-dosing    |        |                               | x                         |            |             |                      |             |                      |             |                      |                        |
| Randomization                                                           |        |                               | x                         |            |             |                      |             |                      |             |                      |                        |
| Training in use of Respimat® (with spacer)                              |        |                               | x                         |            |             |                      |             |                      |             |                      |                        |
| Check study medication compliance                                       |        |                               |                           | x          | x           | x                    | x           | x                    | x           | x                    | x                      |
| Dispense study medication                                   |        |                               | x                         | x          | x           |                      | x           |                      | x           |                      |                        |
| Dispense/Check rescue medication                                        |        | x                             | x                         | x          | x           |                      | x           |                      | x           |                      |                        |
| Collect study medication / Drug accountability                          |        |                               | x                         | x          | x           |                      | x           |                      | x           |                      | x                      |
| Instructions for using the TIPP diary App (PACD  )          |        | x                             |                           |            |             |                      |             |                      |             |                      |                        |
| Review/download TIPP diary App (PACD  )                     |        |                               | x                         | x          | x           | x                    | x           | x                    | x           | x                    | x                      |
| TRACK test                                                              |        | x                             |                           |            | x           |                      |             |                      |             |                      | x                      |
| Caregiver's global impression of change (CGI-C)             |        |                               |                           |            |             |                      |             |                      |             |                      | x                      |
| Assessment of asthma control (GINA)                         |        | x                             | x                         |            | x           |                      | x           |                      |             |                      | x                      |
| Adverse events (AE)                                                     |        | x                             | x                         | x          | x           | x                    | x           | x                    | x           | x                    | x                      |
| Concomitant therapy                                                     |        | x                             | x                         | x          | x           | x                    | x           | x                    | x           | x                    | x                      |
| Trial completion                                                        |        |                               |                           |            |             |                      |             |                      |             |                      | x                      |

1. Hematology and blood chemistry. Topical (percutaneous) analgesia to reduce pain associated with venipuncture, e.g. amethocaine gel or EMLA cream (Eutectic Mixture of Local Anesthetics), must be applied (may only be omitted in patients who explicitly refuse it). A maximum of 3 puncture attempts to obtain blood (approx. 5 mL) will be performed. Visit 1 laboratory parameters comprise: differential blood count, glutamate-pyruvate-transaminase (GPT), glutamate-oxalate-transaminase (GOT), alkaline phosphatase (AP), urea, creatinine levels and total serum IgE and specific IgE to birch, grass, *Dermatophagoides pteronyssinus*, *Alternaria*, *Cladosporium*, cat, dog, hen's egg, cow's milk and peanut. All parameters will be documented in the electronic Case Report Form (eCRF). PaxGene tubes for miRNA will only be sampled at V1.
2. Spirometry/ Oscillometry will only be performed in children  $\geq 4$  years who are capable of providing spirometry / oscillometry of acceptable quality. To confirm acceptable quality, spirometry / oscillometry measurements will be performed in patients  $\geq 4$  years if they are capable of providing measurements of acceptable quality (with a mouthpiece) and if the required equipment is available at site.
3. It is not necessary to perform lung function if the medical files provide clear evidence that the patient is not able to perform technically acceptable lung function. Lung function measurements are performed -10 minutes prior to trial drug administration and 30 minutes post-dose at visit 2 only.
4. Spirometry / oscillometry will be performed -10 minutes prior to trial drug administration and 30 minutes, post-dose at visit 2.
5. Each Respimat® inhaler contains drug supply for 30 days.
6. In order to reduce the burden of parents, the electronic diary does not have to be filled out daily all year round. It is well known from many studies that asthma exacerbations occur particularly in autumn, winter and spring. For this reason, the diary does not have to be kept for 4 months in the months of May, June, July and August. If the patients are recruited in the summer months, they only need to keep an electronic diary between visit 1 and visit 2.
7. The CGI-C should be completed prior to other visit assessments and should precede any discussions with a health professional (physician or nurse).
8. Levels of asthma control will be measured as described in the GINA guideline.
9. The following data are collected during telephone contacts: compliance of study medication use, health status, AEs, concomitant diseases and treatments, concomitant therapies, and medication, and exacerbations.
10. The screening period (between visit 1 and visit 2) may be extended by 7 days (see flow chart), e.g. for administrative reasons.
11. All patients must be symptomatic (partly controlled or uncontrolled) as defined by the GINA guideline for children aged 5 years and younger (7) at visit 1 (screening) and before randomization at visit 2. If this criterion is not met at visit 2, the visit can be repeated once within 2 weeks.
12. In case of severe asthma exacerbation or severe respiratory tract infection (or any other acute illnesses) defined by systemic steroid intake or hospitalization in the 4–6 weeks prior to visit 2, the randomization visit (visit 2) must be postponed until 4 weeks following recovery from the infection or exacerbation.

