**PACD**

The PACD will be used to evaluate daily asthma symptoms in children aged 1–5 years (54). The electronic diary includes various questions that have to be answered in the evening for daytime symptoms and the previous night. The combined daytime score is the average of scores from questions 4–7 in the diary which are questions regarding severity of cough, wheezing, trouble breathing, and interference with activities, scores for each question range from 0 (best) to 5 (worst). Using a symptom diary during 12 months will allow the symptom load of the patients and the asthma severity in treated vs. control patients to be defined and documented. It is preferred the same parent/guardian answers the questions during the study. The PACD questions will be collected electronically by the TIPPDiary app.

In order to reduce the burden of parents, the electronic diary should not be filled out daily all year round. It is well known from many studies that asthma exacerbations occur particularly in autumn, winter and spring. For this reason, no diary should be kept for 4 months in the months of May, June, July and August. If the patients are recruited in the summer months, they only need to keep an electronic diary between visit 1 and visit 2.

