## 7 SAFETY

Safety of the study will be ensured by monitoring of symptom score and rescue medication and lung function. Salbutamol pressurized metered dose inhalers (pMDI) via a spacer as needed will be permitted as rescue medication after visit 1 during observation and after randomization throughout the study.

An asthma exacerbation is defined as an increase of rescue medication (RABA) of more than 6 puffs per day compared to baseline and the use of systemic glucocorticosteroids.

Parents are advised to give in case of a severe asthma exacerbation systemic glucocorticosteroids (Celestamine for 3 days according to manufacture; see table 4 Appendix 15.2) by oral route and contact the investigator within 24 hours.

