## Determination of primary and secondary measures

**The primary efficacy endpoint** is the time to first severe exacerbations defined by hospitalization and/or at least 3 days of systemic steroids or one day of rectal prednisolone (Rectodelt®). Severe exacerbations were chosen as primary outcome because they are patient-important outcomes that have significant consequences for children, caregivers, and the health care system.

**Key secondary endpoint(s) for all patients:** Secondary endpoints for all patients:

- Number of severe exacerbations
- Exacerbation-free survival time defined as the time from randomization until the first severe exacerbation.
- Percentage of patients requiring systemic corticosteroid rescue for asthma during the 52-week treatment period.
- Number of hospitalizations (severe exacerbation).
- Percentage of days and episodes of > 3 days with use of PRN salbutamol rescue medication during 52-week treatment period (non-severe exacerbation).
- Percentage of days without asthma symptoms assessed by TIPP diary App (PACD).
  - A day without asthma symptoms is defined as a day during which the patient experienced no asthma symptoms (daytime and overnight; question 1, 2, 5, 6, did not use rescue medication (salbutamol) (question 3 and 7), and had no asthma exacerbation/worsening requiring systemic corticosteroids, an unscheduled visit to a doctor's office, or hospital (question 11).
- Percentage of night-time awakenings due to asthma symptoms as assessed by the TIPP diary App.
- Health utilization defined as number of physician visits during treatment.
- Number of missed days in daycare.
- Number of asthma-related events defined by use of antibiotics.
- Evaluation of TRACK at V1, at V4 and at end of treatment.
- CGI-C at end of treatment.

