## 15.5 Pediatric asthma caregiver diary (PACD) and instructions

The PACD will be provided as an APP for the caregivers. Daily symptoms will be recorded from visit 1-visit 3 independent from the months of recruitment for 20 weeks. The PACD will be stopped in the summer for 4 months from May-end of August and restarted at the first of September.

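### Footnote 6, section 6.2 and Appendix 15.5 give incompatible diary rules; under the first two, a child recruited in summer has no required on-treatment diary

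*Protocol*

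**What the plan says.** The diary schedule appears in three places.

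- **Trial schedule, footnote 6.** The summer diary is optional: "the diary does not have to be kept for 4 months in the months of May, June, July and August". For summer recruits: "If the patients are recruited in the summer months, they only need to keep an electronic diary between visit 1 and visit 2".
- **Section 6.2, PACD.** The summer instruction is firmer: "no diary should be kept for 4 months in the months of May, June, July and August". The sentence on summer recruits is the same as in footnote 6. The preceding paragraph, however, describes a year-long diary: "Using a symptom diary during 12 months will allow the symptom load of the patients".
- **Appendix 15.5.** "Daily symptoms will be recorded from visit 1-visit 3 independent from the months of recruitment for 20 weeks". Then: "The PACD will be stopped in the summer for 4 months from May-end of August and restarted at the first of September".

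The flow chart marks diary review at visits 2 to 7 and at all three telephone contacts, with no exception for summer recruits.

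On the endpoint side, the bullet on days and episodes of salbutamol use carries an explicit period in sections 3.4, 6.1 and 8.3: "rescue medication during 52-week treatment period (non-severe exacerbation". Symptom-free days and night-time awakenings are assessed by the diary app, but no period is stated for them.

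**The concern.** These are instructions to sites and parents about what to collect. An analysis plan can choose a denominator later, but it cannot recover days that nobody recorded, or undo different practice at 13 sites that followed different pages. A family recruited in June could reasonably stop the diary at visit 2, at visit 3, or pause and restart on 1 September, depending on which page the site used.

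At stake are the diary-based secondary endpoints: how many on-treatment days each child contributes, and whether that number follows one rule. The salbutamol endpoint has a further problem. Its stated 52 weeks cannot be filled from the diary under any of the three rules, because all three release or stop the diary from May to August.

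**Working it through.** **1. The one duration the protocol gives.** Appendix 15.5 puts visit 1 to visit 3 at 20 weeks. Inputs: visit 2 is 4 to 6 weeks after visit 1 (section 5); visits 3 and 4 are 6 and 16 weeks after visit 2 (section 3).

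- Visit 1 to visit 3: (4 to 6) + 6 = 10 to 12 weeks.
- With the ±1 week window at visit 3: 4 + 5 = 9 to 6 + 7 = 13 weeks.
- Adding the 7-day screening extension: 6 + 1 + 7 = 14 weeks. Adding a repeat of visit 2 within 2 weeks: 6 + 1 + 2 + 7 = 16 weeks.
- Visit 1 to visit 4: (4 to 6) + 16 = 20 to 22 weeks.

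The stated 20 weeks is not reproduced for visit 1 to visit 3. It fits visit 1 to visit 4. Only a visit 2 postponed for an exacerbation or acute illness could stretch visit 1 to visit 3 that far.

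**2. Size of the summer pause.** May to August is 31 + 30 + 31 + 31 = 123 days. Over 52 weeks (364 days), 123/364 = 34%, leaving 241/364 = 66%. No child is required to have a full 52-week diary.

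**3. On-treatment diary days required, as a share of 364 days.**

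| Rule | Child recruited May–August | Other children |
|---|---|---|
| Footnote 6 and section 6.2, literal | 0% | about 66% |
| Pause only, same calendar for all | about 66% | about 66% |
| Appendix 15.5 (visit 2 to visit 3 always, plus pause) | 66% to 78% by randomization date | 66% to 78% by randomization date |

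The 0% arises because treatment starts at visit 2, so a diary from visit 1 to visit 2 is entirely pre-treatment. The 78% arises when all 42 days from visit 2 to visit 3 fall in the pause: (241 + 42)/364 = 283/364 = 78%.

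**4. Number of children under the literal rule.** The protocol gives no recruitment pattern by month. Assuming even recruitment over 24 months, with recruitment dated at visit 1, the summer share is 123/365 = 33.7%, and 152 × 0.337 = 51. For an assumed share of 20%, 152 × 0.20 = 30; for 40%, 152 × 0.40 = 61. With even recruitment, mean required coverage is about 0.663 × 66% = 44% under the literal rule, against 66% with the pause alone.

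**The case against.** The strongest reply is that the sentence on summer recruits sets a minimum and can be read in context as an exception to the pause: families recruited while the diary is off still keep it during run-in, and the normal calendar then resumes. The flow chart's diary reviews for everyone, the 12-month purpose in section 6.2 and the 1 September restart in Appendix 15.5 all point that way. This is a fair reading and may be what was intended, but it is not written, and it still conflicts with Appendix 15.5 on visit 2 to visit 3.

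The reply also limits the point. Footnote 6 and section 6.2 are nearly the same paragraph and differ only between optional and not to be kept; the sharp conflict is with Appendix 15.5. The pause itself is a reasoned choice to spare parents, and is not criticised here.

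A reader might infer more than the text supports:

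- *That all diary endpoints are defined over 52 weeks.* Only the salbutamol bullet says so, and that bullet does not name the diary, although the diary collects rescue use daily and the safety text in sections 3.4 and 8.3 refers to rescue medication by electronic diary.
- *That a third of children will have no on-treatment diary data.* The text gives zero required days, not zero days. Entry requires recent symptoms and the protocol places exacerbations mainly outside summer, so a summer share below one third is plausible.
- *That the treatment comparison is biased.* Recruitment month precedes randomization and the trial is double-blind, so calendar gaps fall on both arms alike in expectation. Selective optional summer entries are conceivable, but nothing in the protocol shows them.
- *That safety is unmonitored in summer.* Section 7 says "Safety of the study will be ensured by monitoring of symptom score and rescue medication and lung function" without naming the diary. Adverse events are collected at every visit and call all year, and the calls ask about exacerbations. Much of this is already covered.

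**Conclusion.** The inconsistency is real and should be corrected. The three places cannot all be followed, and the 20 weeks in Appendix 15.5 does not match the visits it names.

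For every child, the pause removes 123 days, about 34% of the treatment period, from an endpoint stated over 52 weeks. For summer recruits, required on-treatment coverage is 0% under footnote 6 and section 6.2 taken literally, and 66% to 78% under Appendix 15.5. The count of about 51 of 152 is a worst case that rests on the literal reading and on even recruitment; a summer share of 20% to 40% gives about 30 to 61.

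The consequence is lost information and an inconsistent observation window for diary-based secondary endpoints. The definition of the primary endpoint and the sample size do not depend on it.

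**What to change.** - Put one rule in footnote 6, section 6.2 and Appendix 15.5: diary from visit 1 to visit 2 for all, then every on-treatment day from 1 September to 30 April whatever the recruitment month. Summer recruits then restart on 1 September, as Appendix 15.5 already provides.
- Correct the visit 1 to visit 3 and 20-week statement in Appendix 15.5, and state whether recording from visit 2 to visit 3 in summer is kept. Dropping it gives every child the same window at about 66% coverage; keeping it raises coverage to at most about 78%, but coverage then depends on the randomization date.
- In the salbutamol bullet only (sections 3.4, 6.1 and 8.3), replace the 52-week period with the on-treatment diary window. Leave the 52-week wording of the systemic-corticosteroid endpoint unchanged, since it is not a diary measure.
- Calculate diary percentages over completed diary days in that window, excluding optional May–August entries. The detail can sit in the SAP, provided the window is fixed in the protocol.

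The cost is amendment wording and an app reminder on 1 September. The price in interpretation is that diary endpoints describe about 8 of 12 months, and this should be said when they are reported.
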